#### Care Partner

Care partner participants will be eligible if they are (1) identified by the patient participant who randomized to the R-D1D intervention group; (2) are 18 years or older; (3) speak and understand English or Spanish; and (4) are willing to participate in a telehealth intervention with the patient participant. Care partners will not be directly recruited.

### Existing D1D Intervention

The intervention is the adapted R-D1D from the existing D1D program. D1D was designed for adults with T1D and T2D and is delivered using a hybrid model that includes in-person small-group and individual DSMES sessions. D1D is delivered by an interdisciplinary faculty specializing in diabetes care, including a nurse practitioner, certified diabetes care and education specialist, pharmacist, exercise specialist, ophthalmology technician, chef, licensed clinical social worker, endocrinologist, and obesity medicine physician. The topics included pathophysiology, complications, screenings, laboratories, medication options, weight management, the importance of exercise, healthy eating, troubleshooting glucose levels, diabetes technology, and healthy coping with diabetes. A healthy breakfast, interactive lunch with a chef demonstration, and snacks were also provided (Multimedia Appendix 1). An emphasis on participants providing education and support to others in the group sessions was encouraged. The participants received written and digital educational materials, recipes, a copy of the Calorie King Book, and resistance bands.

We anticipate R-D1D adaptations may focus on healthy eating based on food available in rural communities, stigma surrounding mental health in rural communities as it relates to diabetes management, and program structure and timing.

### Adapted R-D1D Intervention

R-D1D will be delivered by an interdisciplinary team of health care professionals specifically trained in the D1D program, including a nurse practitioner, physician, registered dietitian, certified diabetes care and education specialist, pharmacist, and a licensed clinical social worker. The R-D1D program will be delivered by telehealth by members of the original D1D team. An overview of the D1D curriculum that will be adapted is detailed in Multimedia Appendix 1.

Intervention group participants will meet with study staff to assess the participant’s technology literacy, test the participant’s internet connection and chosen electronic device, and provide instruction and demonstration for connecting to the videoconference platform. More than 1 meeting may be required. These meetings will be held via the same platform used for R-D1D intervention to allow the opportunity to troubleshoot directly with the participant.

### Control Group

The control group will receive a standard patient education handout that covers the ADCES7 self-care behaviors (healthy coping, healthy eating, being active, monitoring, taking medication, problem solving, and reducing risks) [24].

### Implementation Strategies

Implementation strategies refer to “methods or techniques used to enhance the adoption, implementation, and sustainability of a clinical program or practice” [25]. For this study, we will use several implementation strategies [26], including the following: (1) BCT to adapt and tailor D1D for the rural setting; and (2) technical assistance and workflow design. Grounded in the principles of community-based participatory research, BCT is a process used by partnerships of community members and academic researchers to translate medical information and guidelines into concepts and messages that partnerships believe will be relevant and actionable to local communities [27-30]. Partnerships develop materials and dissemination strategies that use and reflect local culture and assets to effectively move messages and materials to the desired audience. In the traditional BCT, community-academic partnerships are guided by the questions, “What is the message to our community?” and “How do we effectively share these messages with the community?” [31]. The process relies on the community members’ and researchers’ unique expertise, experiences, and perspectives. For this study, a modified BCT process will be used to adapt the existing D1D program for use in rural communities and primary care practices. Telehealth technical assistance will be provided by the community research liaisons or practice facilitators as needed.

### Outcomes and Measures

The outcomes for this study are informed by the Reach, Effectiveness, Adoption, Implementation and Maintenance (RE-AIM) framework [32]. We will use multiple methods (qualitative and quantitative) to assess select RE-AIM domains. Reach and Effectiveness are both patient-level outcomes. Reach refers to the number and percent of eligible patients who participate in the intervention, characteristics of those who participate and complete the measures, and reasons for not participating. Effectiveness refers to clinical and behavioral patient-level outcomes. Adoption, Implementation, and Maintenance are practice-level outcomes (maintenance can also refer to patient-level maintenance of health outcomes over time). Adoption refers to the number, percent, and characteristics of clinical practices who were invited to offer the intervention to their patients who participate in the study. Implementation refers to consistency of delivery of the intervention as intended (ie, fidelity), as well as practice perceptions of the acceptability, appropriateness, and feasibility of delivering the intervention in their clinical practice setting [33]. Maintenance refers to sustained effects on patient outcomes over time and to continued intervention delivery within the clinical setting beyond the study period, which will be explored in a future study.

#### Practice-Level Adoption, Implementation, and Maintenance

We will conduct baseline practice characteristics surveys, practice culture surveys, and individual semistructured interviews with 3 providers or staff at each practice (N=6) to assess practice characteristics and context, perceived value and fit with practice goals and priorities, feasibility (including resources required and perceived burden), and sustainability (including factors influencing interest in continuing to offer R-D1D when available). We will also administer valid, reliable surveys on perceived R-D1D intervention acceptability, feasibility, and appropriateness using the scales developed by Weiner et al [33]. Interviews and surveys will be conducted after each cohort is delivered.

#### Patient-Level Reach

We will capture data on R-D1D attendance, percent of R-D1D sessions attended, R-D1D program satisfaction, and patient reasons for participating and not participating.

#### Patient-Level Effectiveness

For both intervention and control patients, patient-reported outcome measures will include psychosocial (diabetes distress measured via Problem Areas in Diabetes scale [34,35] and Family and Friend Involvement in Adults’ Diabetes [36]), and behavioral (measured via Self-Care Inventory Revised [37]). Patient-level clinical outcome measures will include A_1c_, blood pressure, and BMI. A_1c_ will be obtained by home kit. These data will be collected at baseline and 3-month follow-up.

### Plans to Promote Participant Retention and Complete Follow-up

R-D1D is designed to be completed in 1 day. Study staff will encourage patient participants to participate in the study activities (intervention, follow-up surveys, and interviews) through phone calls, text messages, and email reminders.

### Data Management and Ethics Approval

Data use agreements among participating organizations have been established. The study procedures were approved by the University of Utah Multiple Institutional Review Board on October 28, 2020 (IRB_00133179).

### Statistical Methods and Analyses

#### Quantitative Analysis for RCT

Evaluating Reach will include description of the characteristics of those enrolled and screened ineligible and provide preliminary data on recruitment and retention capabilities for future studies. Quantitative metrics for recruitment and retention rates will inform population point estimates and 95% confidence intervals. For example, a 70% retention of 64 participants leads to a point estimate and CI of 70% (SD 6).

Descriptive statistics will be used to summarize R-D1D reach, adoption, and implementation at the participant and practice level. Special attention will be used to stratify outcome measures based on diabetes type, gender, and clinic site. For quantitative measures on feasibility, appropriateness, and acceptability, we will use the validated scales by Weiner et al [33]. Each of the 3 domains is composed of 4 Likert-scale questions (Completely Disagree 1 to Completely Agree 5). Our benchmarks for success will be to obtain domain means of 4 or greater.

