## Methods

### Design

This study will use the BCT method to adapt the medical information, guidelines, and materials in the current D1D intervention for use with English-speaking and Spanish-speaking people living in rural eastern Colorado (R-D1D). Then, using a 1:1 type 2 hybrid trial, we will conduct a pilot test in 64 total patients from 2 practices to compare R-D1D to a standard education control. Acceptability and feasibility of R-D1D will be assessed at the patient and practice levels.

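### The worked retention example prints one standard error (6 points) where a 95% confidence interval is promised; the 95% half-width is about 11 points

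*Protocol article*

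**What the plan says.** The protocol article, section Quantitative Analysis for RCT, states the aim as follows: "Quantitative metrics for recruitment and retention rates will inform population point estimates and 95% confidence intervals". The next sentence is offered as an example of that aim: "a 70% retention of 64 participants leads to a point estimate and CI of 70% (SD 6").

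The denominator is not in doubt. The Design section says "we will conduct a pilot test in 64 total patients from 2 practices", and Group Randomization builds the same total from two sites with four groups of 8 each (2 × 4 × 8 = 64).

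The article gives no other precision figure for any estimate, and no power calculation.

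**The concern.** The example follows directly on a promise of 95% intervals, so a reader will take the 6 as the margin of a 95% interval. A margin of 6 points looks too small for a proportion near 70% in 64 people.

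The same section says that the pilot will supply preliminary information on recruitment and retention for later studies. How well retention is estimated is therefore part of what the pilot is meant to deliver. If the example were followed as a template at analysis, the reported intervals would be about half as wide as a 95% level requires.

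**Working it through.** **Inputs**
- Retention proportion p = 0.70 (illustrative; Quantitative Analysis for RCT).
- Number of participants n = 64 (Design; Group Randomization).
- Confidence level 95% (Quantitative Analysis for RCT). Sidedness is not stated; two-sided is assumed.
- Stated spread: 6 points, in the phrase "point estimate and CI of 70% (SD 6").

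**Step 1: reproduce the printed 6.**
SE = sqrt(p(1 − p)/n) = sqrt(0.70 × 0.30/64) = 0.0573, or 5.7 points. This rounds to 6, so the printed figure is one standard error.

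**Step 2: the 95% interval.**
The Wald half-width is 1.96 × 0.0573 = 0.112, or 11.2 points. The interval is 70 ± 11.2, that is 58.8% to 81.2%.

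**Step 3: does another standard method give 6?**
Because 70% of 64 is 44.8, not a whole number, the exact interval is shown for both neighbouring counts.

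| Method | Limits | Half-width (points) |
|---|---|---|
| Wald, 95% | 58.8% to 81.2% | 11.2 |
| Wald with continuity correction, 95% | 58.0% to 82.0% | 12.0 |
| Wilson at p = 0.70, 95% | 57.9% to 79.8% | 11.0 |
| Exact, 44/64, 95% | 55.9% to 79.8% | 11.9 |
| Exact, 45/64, 95% | 57.6% to 81.1% | 11.8 |
| Wald, 90% two-sided (same multiplier as one-sided 95%) | 60.6% to 79.4% | 9.4 |
| Wald, 80% two-sided | 62.7% to 77.3% | 7.3 |

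None of these gives 6.

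**Step 4: what plus or minus 6 would mean.**
- Ratio of half-widths: 11.2/6 = 1.87, so the printed figure is about 0.53 of the correct one.
- Nominal confidence: 0.06/0.0573 = 1.05 standard errors, which corresponds to about 70% two-sided.
- Sample size for a 95% half-width of 6: 0.21 × (1.96/0.06)² ≈ 224 participants, against 64.

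**Step 5: the SD label.**
The standard deviation of a yes/no variable with p = 0.70 is sqrt(0.70 × 0.30) = 0.458, or 45.8 points. Read literally as an SD, the 6 is also wrong.

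**The case against.** The best defence is that the sentence may be a labelling slip and not a miscalculated interval. The SD label may have replaced a plus/minus sign, or a standard error may have been meant. If a standard error was meant, the 6 is right, and no false 95% limits were ever claimed; the article does not print 64% to 76% anywhere. This stands as a reason not to call it a definite claim of false precision. It does not rescue the sentence. With a plus/minus sign, the figure is an interval of about half the proper width. As a standard error, it carries two wrong labels and the promised 95% interval is absent.

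It is also fair to say that the operative commitment, to 95% intervals, is stated correctly in the preceding sentence. Intervals computed properly from the observed data would be unaffected by a faulty illustration.

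A reader might go further in two ways that the document does not support.
- **That the trial's size or success criteria are compromised.** The article justifies 64 only as suitable for iterating the intervention (Patient and Care Partner, under Sample and Recruitment). It sets no retention threshold. The one numerical benchmark in the section is a mean of 4 or more on the feasibility, appropriateness and acceptability scales.
- **That the next trial's dropout allowance will be wrong.** The article gives no such calculation. Patient Level Effectiveness Analysis ties the size of a future study to estimated standard deviations, and retention is described only as preliminary information.

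**Conclusion.** The example is wrong as printed on every reading. The 6 is one standard error (5.7 points, rounded), shown under the labels CI and SD. The 95% half-width is about 11 points (11.0 to 12.0 across the standard methods), so the example, taken as a confidence interval, is about half the correct width.

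This rests on p = 0.70 and n = 64 as stated, a two-sided 95% level, and participants treated as independent.

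It is a minor correction to a stated precision figure. It does not bear on the sample size, the benchmarks or the randomised comparison.

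**What to change.** Replace the example with a sentence such as: *70% retention of 64 participants gives a 95% confidence interval of about 59% to 81% (Wald, half-width 11 points).* If the Wilson method is to be used, give about 58% to 80% instead. Either method is acceptable; the limits printed should match the method used. Remove the SD label, and do not carry plus or minus 6 forward as the pattern for reported intervals.

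The cost is one sentence and a less favourable stated precision. Nothing in the design changes.

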#### Patient Level Effectiveness Analysis

Descriptive statistics will be used for intervention and control groups at baseline and 3 months stratified by language including outcomes from (1) surveys assessing diabetes distress as measured by the Problem Areas in Diabetes (PAID) scale and behavioral diabetes self-care as measured by the Self Care Inventory-Revised Version (SCI-R); and (2) clinical measures including A_1c_, blood pressure, and BMI. We will estimate population standard deviations so as to determine the sample size needed for a fully powered study to test for clinically meaningful improvements in outcomes [38,39]. Exploratory mixed-effects models using maximum likelihood estimation will be used to examine change between baseline and 3 months comparing intervention and control groups. This analysis is in keeping with an intent-to-treat standard and allows the use of all available data for analyses regardless of missing data. Combined, the results from this study will provide an initial indication of patient-level effectiveness as a clinically meaningful treatment effect in preparation for a larger effectiveness trial.

#### Missing Data

Missing Values Analysis tools will be used to describe if there are patterns to missing data. However, for the mixed models with random effects and maximum likelihood, it is not necessary to eliminate observations from participants who subsequently drop out, nor is it necessary to impute individual observations. To minimize loss of scale scores due to missing items in a computed scale such as PAID and SCI-R, we will prorate the respondents’ score based on their answered items. If a respondent is missing more than 30% of the items in a computed score, we will code the scale score as missing, thereby ensuring psychometric validity.

#### Qualitative Analysis

Qualitative descriptive analysis will be used to evaluate practice provider and staff interviews. Audio-recorded interviews with participants and practice providers or staff will be transcribed. Using standard qualitative content analysis, all investigators will review data, codes, and categories. Matrices will be used to organize codes by demographic variables (diabetes type, gender, and clinic site), patient reach, and practice-level adoption and implementation. Overarching themes will then be developed. Qualitative and quantitative data will then be triangulated to assess the R-D1D intervention.

#### Data Monitoring

The study team has developed data collection protocols to ensure maximum compliance and protection of informed consent documents, surveys, personal health information, and audio-recorded sessions (for interviews). The participants will complete electronic surveys via a weblink to REDCap (Research Electronic Data Capture), a HIPAA-compliant web-based application hosted at the University of Utah Center for Clinical and Translational Science, which will securely store and protect data. No names will appear on the surveys; however, the survey data will be linked to a practice location using an identification number. Survey data will be confidential and will only be used by the study team.

Interviews with practice staff will be conducted by the research team and will be recorded and transcribed with the respondent’s permission. No protected health information will be collected from the interviews, and all data will be de-identified. All audio files from the interviews will be stored on a secure server maintained by the University of Utah College of Nursing information technology team, and only the study team will have access to the data.

Data collected from the medical chart (ie, A_1c_, blood pressure, and BMI) or by phone (if participants are unable to complete electronic surveys) will be hand-entered by trained practice facilitators. Audio recordings of the participant interviews will be stored securely in a shared file system that only the study team will have access to. This file system will be backed up continuously and protected by the University of Utah firewalls.

A_1c_ data will be collected using home A_1c_ kits, which require 4 drops of blood (similar to checking a glucose level). The participants will mail the A_1c_ kits directly to the laboratory and will be tracked with a tracking number to ensure privacy and will allow the study team to link the data to the participant once the A_1c_ has been processed.

#### Harms

Risk of harm to participants (patient, practice, and staff) is minimal. Should any harm occur, it will be reported to all involved institutional review boards and the data safety monitoring team in accordance with institutional and federal policies.

## Results

We completed BCT [40] and have begun recruiting participants for the RCT component of the study. This study is expected to conclude in July 2022.

## Discussion

R-D1D will be developed in collaboration with patients with diabetes and other community members living in rural communities, providers and staff from participating practices, and academic clinician-researchers and their research teams.

While rural residents are burdened by higher rates of diabetes compared to their urban counterparts, it is difficult to access diabetes specialty care in rural areas. There is a critical need to test interventions to address diabetes health disparities in rural areas, in partnership with primary care practices, where the majority of people with diabetes receive their diabetes care in these areas. This study will adapt the D1D program, an effective, time-efficient diabetes self-management education and support program for adults with diabetes at University of Utah, for delivery in English and Spanish to rural residents of Eastern Colorado. Feasibility and acceptance will be evaluated. If successful, this project has potential for improving diabetes care nationally, not just for the residents of Colorado.

This project can provide valuable information on a program of research that is innovative and timely and has the potential to impact the delivery of diabetes specialty care in Spanish and English for rural regions beyond Colorado.

## Appendix

Multimedia Appendix 1 Comparison of the existing D1D (Diabetes One-Day) intervention and the adapted R-D1D (Rural Diabetes One-Day) intervention.

## Abbreviations

BCT: Boot Camp Translation
D1D: Diabetes One-Day
DSMES: diabetes self-management education and support
HIPAA: Health Insurance Portability and Accountability Act
PAID: Problem Areas in Diabetes
R-D1D: Rural Diabetes One-Day
RCT: randomized controlled trial
RE-AIM: Reach, Effectiveness, Adoption, Implementation, and Maintenance
REDCap: Research Electronic Data Capture
SCI-R: Self-Care Inventory-Revised Version
T1D: type 1 diabetes
T2D: type 2 diabetes
